**Figure 1 f1:**
[figure not shown]
Flow chart.

### Data Collection and Follow-Up

#### Pre-Operation

Data on maternal age, parity, gravida, gestational sac age at diagnosis, the size of sac, and the number of previous cesarean section (including the indications of cesarean section) will be collected. The subtypes of cesarean scar pregnancy (Types 1 and II and III) detected by ultrasound findings following a guideline (16) will be classified. In addition, the QRS score for predicting blood loss will be also calculated based on our recently developed quantitative risk-scoring system (13).

#### Intraoperative

Duration of operation, intraoperative blood loss and intraoperative complications including emergency treatment due to the failure of first line options and modifications of treatment will be recorded. All the tissues after the operation will be sent to the department of pathology to exclude hydatidiform mole.

#### 6-Month Follow-Up Visit

Recovery of the endometrium (menstrual cycle) will be monitored by ultrasound on a routine basis. For patients who receive the treatment with UAE, liver and kidney functions will be tested one week after the operation. Cesarean scar niche will also be examined by ultrasound at 3 and 6 months.

#### 2-Year Follow-Up

Subsequent pregnancy, subsequent fertility, outcomes of subsequent pregnancy including recurrent cesarean scar pregnancy and live births will be recorded.

### Primary Outcomes

Comparisons of duration of operation, intraoperative blood loss and intraoperative complications between treatments by ultrasound guided suction curettage with or without UAE.The numbers of cases that receive emergency hysteroscopic and/or laparoscopic resection.Retrospectively analyze the intraoperative blood loss, taking into account the subtypes of cesarean scar pregnancy.Retrospectively validate the QRS score to predict intraoperative blood loss.

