**Methods and Analysis:**

We propose undertaking a randomized clinical trial sequentially recruiting 200 patients. All the patients will randomly receive ultrasound guided curettage with or without UAE. Data on the subtypes of cesarean scar pregnancy (Types 1 and II and III) detected by ultrasound will be collected before operation. The score on estimating intraoperative blood loss assessed by our recently developed quantitative risk-scoring system (QRS) will be collected before the operation. We will primarily compare the duration of the operation, intraoperative blood loss, and complications between the two groups. We will also retrospectively analyze the association of subtypes of cesarean scar pregnancy and the options of treatment and validate the QRS score. Outcomes of subsequent pregnancy within the 2-year follow-up will be secondary outcomes.

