### Statistical Analysis

All the data will be expressed as mean and SD. Student t-test or ANOVA will be performed when appropriate using Prism software version 8.4. Two side p value of less than 0.05 will be considered statistically significant.

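### Several unranked primary outcomes share one undivided p<0.05 rule, although the trial is sized for a single test of blood loss above 300 ml

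*Protocol article*

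**What the plan says.** All references are to the protocol article.

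- **Primary Outcomes** begins with three comparisons between arms: "Comparisons of duration of operation, intraoperative blood loss and intraoperative complications between treatments by ultrasound guided suction curettage with or without UAE". It then adds "The numbers of cases that receive emergency hysteroscopic and/or laparoscopic resection", "Retrospectively analyze the intraoperative blood loss, taking into account the subtypes of cesarean scar pregnancy" and "Retrospectively validate the QRS score to predict intraoperative blood loss". Nothing in the list is ranked or singled out.
- **Statistical Analysis** gives the only decision rule: "Two side p value of less than 0.05 will be considered statistically significant". The tests named are the t-test and ANOVA.
- **Sample Size Calculation** rests on one binary outcome, the proportion of patients losing more than 300 ml. It uses a 5% significance level, 90% power, 200 patients in two equal groups and a detectable difference of 20%.
- **Abstract, Methods and Analysis** gives a shorter list, also unranked: "We will primarily compare the duration of the operation, intraoperative blood loss, and complications between the two groups".
- **Introduction and Discussion** describe the main purpose as judging whether UAE is needed to control intraoperative blood loss.
- **Data Collection and Follow-Up, Intraoperative** records "intraoperative complications including emergency treatment due to the failure of first line options", so emergency treatment already counts among the complications.

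**The concern.** The sample size fits a trial with one primary test. The outcome list describes a trial with several, and the significance rule does not connect the two. Two things are at stake.

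First, the error rate. If duration, blood loss, complications and emergency resection are each tested at 0.05 and any one of them may be reported as the primary result, the chance of a false primary claim exceeds the 5% used for the sample size.

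Second, the trial's answer. UAE might shorten the operation without reducing bleeding, or lower mean blood loss without changing the proportion above 300 ml. The article does not say which result would decide whether UAE is needed, so the choice could be made after the data are seen.

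**Working it through.** **1. Reproduce the protocol's own figure.** Inputs from Sample Size Calculation: mean 184 ml, SD 313 ml, cut at 300 ml, two-sided 5%, 90% power, 1:1 allocation. The 20% is read as percentage points and as a reduction, which is how the section frames it: 35% versus 15%.

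- Rate above 300 ml: z = (300 − 184)/313 = 0.371, and 1 − Φ(0.371) = 35.5%. The protocol says about 35%.
- Patients per arm (pooled, no continuity correction): n = [1.960·√(2·0.25·0.75) + 1.282·√(0.35·0.65 + 0.15·0.85)]² / 0.20² = (1.200 + 0.764)² / 0.04 = 96.4, so 97 per arm and 194 in total.
- Power at 100 per arm: Φ[(0.20·√100 − 1.200)/0.596] = Φ(1.342) = 91.0%.

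The stated 200 is therefore reproduced, but as the size for **one** test at an undivided 5%.

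**2. Count the treatment comparisons.**

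| Listed item | Comparison between arms? |
|---|---|
| Duration of operation | Yes |
| Intraoperative blood loss | Yes |
| Intraoperative complications | Yes |
| Emergency resection | Yes, but overlaps with complications |
| Blood loss by subtype | Re-analysis of blood loss, no test specified |
| QRS validation | No: a question of predictive accuracy |

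The treatment family is three comparisons, or four if emergency resection is tested separately.

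**3. Chance of at least one false positive** when UAE has no effect on any of them and any one result counts.

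- Independent tests, 1 − 0.95^k: k = 3 gives 14.3% and k = 4 gives 18.5%.
- Correlated tests, from a simulation of 1,000,000 draws of equally correlated normal test statistics. The article gives no correlations, so these are assumptions.

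| Correlation | k = 3 | k = 4 |
|---|---|---|
| 0 (formula) | 14.3% | 18.5% |
| 0.5 | 12.6% | 15.6% |
| 0.7 | 10.9% | 13.0% |
| 0.9 | 8.3% | 9.3% |

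Even at a correlation of 0.9 the figure stays above 5%.

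**4. Cost of keeping several primaries.** With a Bonferroni split and the same 35% versus 15%, 90% power needs 250 patients for k = 3 (0.05/3 = 0.0167 each) or 264 for k = 4 (0.05/4 = 0.0125 each). With 200 patients, power for the blood-loss test would be about 81% or 79%.

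**The case against.** The strongest reply has three parts.

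**Blood loss already has priority.** It is the stated aim in the Introduction and Discussion, it is in the primary list, and the sample size uses the same variable. This largely stands. A reader might infer that no listed primary is the outcome used for sizing. That goes too far: the list names blood loss but omits the 300 ml cut. Even so, the section that fixes the primary outcomes does not give blood loss precedence.

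**Multiplicity rules may sit in an analysis plan that is not shown.** This also stands, and the lack of an adjustment method is not the point here. Which outcome is primary is a protocol matter, and the article gives it a section of its own.

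**The size depends on how one counts.** A reader might treat all six items as separate 5% tests, which gives 1 − 0.95^6 = 26.5%, about five times nominal. The document does not support this: QRS validation tests no treatment hypothesis, the subtype item reuses the blood-loss data, and emergency resection overlaps with complications. Calling the outcomes co-primary would mislead as well. The term usually means that all must succeed, which does not inflate the error, and the article states neither rule.

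A reader might also take "We will also retrospectively analyze the association of subtypes of cesarean scar pregnancy and the options of treatment and validate the QRS score" as demoting the subtype and QRS analyses to exploratory. The abstract does not say so; the only outcomes it calls secondary are those of a subsequent pregnancy.

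**Conclusion.** The point holds in a limited form. Several primary outcomes are listed without ranking, three or four of them overlapping comparisons between arms. They share one undivided 0.05 threshold, while the trial is sized for a single test of the proportion losing more than 300 ml.

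The chance of a false primary finding is about 14-19% with independent tests and about 11-16% at correlations of 0.5-0.7. Both ranges are conditional on a rule that any one significant result suffices. That rule is an assumption, as are the correlations. If all outcomes had to succeed there would be no inflation, but power would be lower than for the single test on which the trial was sized. Because the article does not choose between these readings, it also gives no way to settle conflicting results.

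This should be corrected. It does not undermine the randomised comparison itself.

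**What to change.** Name one primary outcome: the proportion of patients with intraoperative blood loss above 300 ml, compared between arms with a test of proportions at two-sided 5%. Add that test to the Statistical Analysis section, which at present names only the t-test and ANOVA. Move duration, blood loss in ml, complications and emergency resection to the secondary outcomes, reported with 95% confidence intervals. Label the subtype and QRS analyses secondary or exploratory, and align the abstract.

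The sample size of 200 then stands, with about 91% power for 35% versus 15%. This takes the protocol's 35% as given; whether its normal approximation is a sound basis for that rate is a separate question.

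A fixed testing order, or a split of the 5% with the larger sample shown above, would also settle the matter. The single primary is the cheapest option and matches both the stated aim and the sizing. Its costs are that the demoted outcomes lose primary status, one analysis method has to be added, and the registry entry, which was not available for this review, may need updating.

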Pre-assessment of blood loss is very important to gynecologists. Our recent study reported that gestational age of cesarean scar pregnancy and blood flow around the site of the gestational sac detected by ultrasound are risk factors for potential intraoperative blood loss (13). We then developed a risk-scoring system (**Table 1**) to estimate intraoperative blood loss, and we found that women with a total score higher than three have a risk for intraoperative blood loss (13). A previous study also used a color Doppler scoring system to estimate intraoperative blood loss, according to vascularization of the pregnancy, and it indicated that women with a higher score have a higher risk of intraoperative blood loss (12).

**Table 1 T1:** Risk-scoring system for the prediction of compression hemostasis requirement.

Variable	Score
Vascularity around the gestational sac*	
No obvious blood flow	0
Sparse or sporadic blood flow	1
Vessel looks like short-columnar pattern	2
Vessel looks cord-like pattern	3
Massive blood flow or arteriovenous fistula	4
Pregnancy duration	
≤40 days	0
41–50 days	1
>50 days	2

*As demonstrated on a color Doppler ultrasonography.

There is currently no randomized clinical trial to compare the intraoperative blood loss and postoperative outcomes by surgical treatment such as ultrasound guided curettage with or without UAE in women with cesarean scar pregnancy. Therefore, we will run a randomized clinical trial to primarily investigate whether UAE is overused in controlling intraoperative blood loss in clinical practice. We recently established a risk-scoring system (QRS) to estimate intraoperative blood loss (13), and we will then retrospectively validate the role of QRS in estimating intraoperative blood loss in this randomized clinical trial with a relatively large sample size. Recently a number of studies reported potential complications in a subsequent pregnancy in women who received surgical treatment (14). Whether the complications in a subsequent pregnancy are related to the options of the previous treatment is unknown. Therefore, the secondary measurement of this randomized clinical trial is to follow up the outcomes in a subsequent pregnancy in women treated by ultrasound guided curettage with or without UAE.

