### Participants

#### Sample Size Calculation

The sample size calculation was based on the reduction of the proportion of cases who lost more than 300 ml of blood during operation. Our recent study (15) showed intraoperative blood loss with a mean of 184 ml and a standard deviation (SD) of 313 ml. Converting to a Z-score, about 35% of cases would have more than 300 ml of intraoperative blood loss. With 90% power at the 5% significance level, recruiting 200 cases in total, we will be able to detect a difference of 20% between two groups.

Therefore, in this randomized clinical trial, 200 women newly diagnosed with cesarean scar pregnancy will be recruited within three years and equally divided into two groups.

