## Discussion

Interventions for cesarean scar pregnancy could cause a massive intraoperative blood loss due to the highly vascular nature of the site of pregnancy. This consequently results in using UAE as one of the options to prevent intraoperative blood loss in clinical practice. However, a recent retrospective study suggested that UAE may be overused in clinical practice (11). Therefore, in this randomized clinical trial, we primarily aim to evaluate the necessity of UAE as a treatment option for cesarean scar pregnancy in order to control the intraoperative blood loss. We will then retrospectively take into account the subtypes of cesarean scar pregnancy to understand whether the optimal options are dependent on the subtypes of cesarean scar pregnancy.

Pre-assessment on predicting intraoperative blood loss which may be dependent on the size and/or site of the sac and the gestational age will help gynecologists select an optimal option for cesarean scar pregnancy treatment. A recent retrospective study used crossover sign (COS) to predict blood loss in surgical treatment (17), suggesting that the crossover sign (COS) is an independent risk factor for severe blood loss during treatment of cesarean scar pregnancy (18). We also recently developed a risk-scoring system (QRS) to estimate blood loss during surgical treatment with a 93.8% sensitivity and 6.3% false negative (13), which has some similarities with the COS system. Due to the relatively small sample size in our previous study, therefore, in this randomized clinical trial with a relatively large sample size, we will retrospectively validate the role of the QRS score in estimating intraoperative blood loss. We hope that this study will generate sufficient evidence for optimal cesarean scar pregnancy treatment. If effective, we believe the QRS score can be a cost-effective and safe tool to estimate intraoperative blood loss in order to reduce the unnecessary use of UAE in clinical practice.

In addition, whether recurrent cesarean scar pregnancy and the outcomes in a subsequent pregnancy including complications,and subsequent fertility in women treated for cesarean scar pregnancy are associated with their previous treatment has not been described well in literature. We hope that the secondary outcomes of the study can provide some useful information on the outcomes of a subsequent pregnancy.

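### The subtype question is a treatment-by-subtype question, but the plan names no interaction test, no exploratory status and no use of the baseline risk factors it collects

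*Protocol article*

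**What the plan says.** - **Primary Outcomes** includes this item: "Retrospectively analyze the intraoperative blood loss, taking into account the subtypes of cesarean scar pregnancy".
- **Discussion** gives its purpose: "to understand whether the optimal options are dependent on the subtypes of cesarean scar pregnancy".
- **Statistical Analysis** gives the method for all data: "Student t-test or ANOVA will be performed when appropriate using Prism software version 8.4". The decision rule is "Two side p value of less than 0.05 will be considered statistically significant". The section mentions no interaction, no covariate and no exploratory label.
- **Introduction** reports from the group's own study that "gestational age of cesarean scar pregnancy and blood flow around the site of the gestational sac detected by ultrasound are risk factors" for blood loss. These two factors make up the QRS in Table 1.
- **Pre-Operation** records subtype (three types) and states that "the QRS score for predicting blood loss will be also calculated". The only analytic use given for the score is validation of its own prediction.
- **Sample Size Calculation** concerns the overall two-arm comparison only: "With 90% power at the 5% significance level, recruiting 200 cases in total, we will be able to detect a difference of 20% between two" (that is, the treatment groups).

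**The concern.** Whether the better option depends on subtype is answered by comparing the UAE effect between subtypes. The plan ranks this question among the primary outcomes, calls the analysis retrospective, and leaves the choice of t-test or ANOVA to be settled as seems suitable, under a single 0.05 rule. Nothing in that wording steers the analyst towards an interaction test rather than a row of within-subtype p-values.

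The row of p-values is the risky route. Each subtype holds only part of a sample sized for the whole, so some subtypes will tend to reach significance and others not, even when UAE works equally well in all of them. Such a pattern is easily read as showing that UAE is needed in one type only, which bears directly on the trial's aim of identifying unnecessary UAE.

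A second, smaller point is precision. The plan names predictors of blood loss and collects them before operation, but the stated treatment comparison makes no use of them.

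**Working it through.** **Inputs from the protocol article:** 35% of cases above 300 ml, a 20-point difference, 90% power, two-sided 5% and 200 women divided equally (Sample Size Calculation and Statistical Analysis); an earlier study that "showed intraoperative blood loss with a mean of 184 ml and a standard deviation (SD) of 313 ml"; three subtypes (Pre-Operation).

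**Assumed, because the article does not give them:** the subtype shares, and the R-squared of the baseline factors for blood loss.

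**1. The plan's own figure.**
- The normal tail at (300 − 184)/313 = 0.371 is 35.5%, matching the stated 35%.
- For 35% against 15%, n per arm = [1.960·√(2·0.25·0.75) + 1.282·√(0.35·0.65 + 0.15·0.85)]² / 0.20² = (1.200 + 0.764)² / 0.04 ≈ 96.4. This rounds up to 97 per arm, or 194 in total.
- With 100 per arm, power is 91%. The stated 200 therefore reproduces, for the overall comparison only.

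**2. Separate tests within subtype, with the same true effect (35% to 15%) in all three.** Power is the exact binomial power of the uncorrected chi-square test. The chance that at least one subtype is significant and at least one is not is 1 − Πpᵢ − Π(1 − pᵢ).

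| Assumed women per arm by subtype | Power of each test | Chance of disagreement |
|---|---|---|
| 33 / 33 / 33 | 48.5% each | 1 − 0.485³ − 0.515³ = 1 − 0.114 − 0.137 = 75% |
| 50 / 35 / 15 | 65%, 49%, 25% | 1 − 0.081 − 0.133 = 79% |

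**3. The same check on blood loss in ml.**
- The difference that 100 per arm detects with 90% power is 313·√(2/100)·(1.960 + 1.282) = 44.3 × 3.242 = 143.5 ml.
- Simulation (200,000 runs, normal theory, SD 313 in every subtype) with a uniform 143.5 ml effect gives disagreement in 75% of trials with equal shares, 77% with 50/30/20% and 80% with 45/45/10%.
- With no UAE effect at all, at least one of three tests is significant in 1 − 0.95³ = 14% of trials.
- A test of treatment-by-subtype heterogeneity gives a false subtype difference in 5% of trials in each of these cases.

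**4. What the interaction test can show.** Take two equal subgroups as a simple case.
- The SE of the interaction is 313·√(4/50) = 88.5 ml, twice the 44.3 ml of the main effect.
- A difference of 88.5 × 3.242 = 287 ml between subgroup effects is needed for 90% power. A difference of 143.5 ml has about 37% power.

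**5. Precision from adjustment.** The SE shrinks by √(1 − R²), and the equivalent unadjusted sample is 200/(1 − R²).
- R² = 0.2: 143.5 × 0.894 = 128 ml, equivalent to 250 women.
- R² = 0.4: 143.5 × 0.775 = 111 ml, equivalent to 333 women.

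These gains are for blood loss in ml. No gain is computed for the proportion above 300 ml.

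**The case against.** A reader might infer that the plan commits itself to separate within-subtype tests, or that its named methods cannot answer the subtype question. The article supports neither reading. A two-way ANOVA with treatment, subtype and their interaction is an ANOVA and tests exactly what the Discussion asks. Nowhere does the article say that t-tests will be run within types or that the ANOVA is one-way. The 75% to 79% is therefore conditional on a choice the plan leaves open, and it rests on assumed subtype shares.

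A reader might also infer that leaving out covariates makes the main comparison wrong. It does not: an unadjusted comparison in a 1:1 randomised trial is valid, and adjustment is a gain in efficiency. The size of that gain is uncertain. The article gives no R-squared, Table 1 is titled for the need for compression hemostasis rather than for blood loss in ml, and this trial is itself meant to validate the score.

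Model details and covariate lists are often left to a full protocol or SAP, and neither is shown. That explains the silence in part. What remains is that the article itself ranks an effect-modification question as primary and states a method family and one significance rule that leave the weaker analysis open.

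The remedy has limits too. The interaction has low power. With 15 women per arm in a small subtype, the UAE arm would expect about 2 events (15 × 0.15 = 2.25), with a 9% chance of none (0.85¹⁵), so a logistic interaction could be unstable.

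**Conclusion.** The point holds as a gap that should be closed and as an improvement that needs no new data, not as an invalid analysis. The article asks a treatment-by-subtype question at primary level without naming the contrast that answers it or marking the answer as exploratory. If separate subtype tests were used, discordant significance under a uniform effect would occur in about 75% to 79% of trials on the binary outcome and 75% to 80% on blood loss in ml, against a 5% false-positive rate for an interaction test. All of these depend on assumed subtype shares. The precision forgone by not adjusting, about 143 ml against 128 to 111 ml, depends on an assumed R-squared of 0.2 to 0.4.

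**What to change.** In Statistical Analysis:

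1. Pre-specify the treatment comparison of blood loss as a linear model (ANCOVA) with treatment, QRS score (or its two components) and subtype.
2. Analyse loss above 300 ml with the same covariates, reported as a standardised risk difference.
3. Answer the subtype question by adding treatment-by-subtype to the blood-loss model. Report the interaction p-value and subtype-specific effects with 95% confidence intervals.
4. Label this analysis exploratory because of its low power, and make no claims of significance within a subtype.
5. Do not rely on a logistic interaction for loss above 300 ml where subtype cells are sparse.

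The cost is a change of wording and a little more analysis work. The covariates are already recorded before operation, and neither the sample size nor the conduct of the trial changes.
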